**Survey Protocol**

| **Protocol Title:** | Survey protocol for the study called : **Knowledge and awareness of human papillomavirus infection and human papillomavirus vaccine among Kazakhstani women attending gynecological clinics** |
| --- | --- |
| **Institution/Affiliation:** | Nazarbayev University  <https://nu.edu.kz/> |
| **Principal Investigator Name/Contact Information:** | [name]  [[contact]](mailto:[contact]) |
| **Sub Investigator(s) Name/Email:** | [name] [contact]  [name] [contact]  [name] [contact]  [name] [contact]  [name] [contact]  [name] [contact]  [name] [[contact]](mailto:[contact]) |
| **Study Contact Person Name/Email:** | [name]  [[contact]](mailto:[contact]) |
| **Locations of survey:** | Obstetrics and Gynecology Department, Keruen Medicus Clinic, Almaty 050040, Kazakhstan;  Obstetrics and Gynecology Department, East Kazakhstan Regional Hospital, Oskemen 07000, Kazakhstan;  Regional Perinatal Center, [name], Aktobe 030006, Kazakhstan;  Obstetrics and Gynecology Department, City polyclinic #6, Nur-Sultan 010000, Kazakhstan;  Gynecology Department, Daliya Clinic, Pavlodar 140013, Kazakhstan |
| **Rationale:** | Although cervical cancer remains one of the top causes of cancer-related morbidity and mortality all over the world, there are no currently published studies to assess the knowledge of HPV and cervical cancer in Kazakhstan. |
| **Primary Objectives:** | The aim of this study is to assess the awareness about HPV, the knowledge of HPV as a cause of cervical cancer, and the awareness of HPV vaccination among Kazakhstani women visiting gynecological clinics in five different parts of the country and to identify the factors associated with the awareness of HPV and HPV vaccine, and knowledge of HPV as a major cause of cervical cancer. |
| **Primary Endpoint:** | Outcome variables for this study are the following: awareness of HPV (“Have you ever heard about HPV vaccine?” Yes/No); knowledge of HPV as a major cause of cervical cancer (“HPV infection is the major cause of cervical cancer.” True/False); awareness of HPV vaccine (“There is a vaccine against HPV infection.” True/False). |
| **Study Design:** | Five doctors ([name], [name] [name], [name], [name]) will be hired to conduct a survey among  women visiting gynecological clinics. The doctors will have training from research team and from TRAINING AND RESOURCES IN RESEARCH ETHICS EVALUATION. The doctors will be trained how to recruit the participants and how to conduct a survey, and how to store completed questionnaires.  At the end of the appointment doctors will propose their patients to participate in the study.  Before participating in the survey prospective respondents will be provided information about research and doctors will read them verbal consent. Verbal consent will be used in the study.  Particularly for this research verbal consent will be used as way to receive informed consent from a participant. As anonymity of the study participants is our primary concern, verbal consent is deemed as most appropriate. Moreover, no personal information related to any of the patients will be made available to the Investigators at any time before, during or after the study. All the information about the study and participants rights will be stated both orally and on the information letter provided to the participants.  Once the respondent agrees to participate in the study, paper based questionnaires will be given to patients. There will be two types of questionnaires utilized to collect data on patient’s medical gynecological history and awareness and knowledge of HPV, and awareness of HPV vaccination. The first questionnaire will be filled out by doctors and consist of 30 items and include the following patient information: socio-demographic characteristics, lifestyle characteristics, and the history of gynecological diseases. The second questionnaire will be filled out by the respondents. The patient questionnaire will consist of 25 items and include the following information about the patients: socio-demographic characteristics, awareness of cervical cancer and the associated risk factors, awareness of screening for cervical cancer, whether the patient had gone through screening for cervical cancer, awareness of HPV, awareness of risks of HPV, and awareness of HPV vaccine.  Doctors and patients will fill out the questionnaires right after the appointment. For doctors it will take approximately 5 mins to complete the questionnaire. For patients it will take approximately 15 minutes to complete the questionnaire.  To keep anonymity survey respondents will be given IDs. Respondent ID will be written on both questionnaires.  Once completed the respondents will return completed survey to the doctor. The doctor will keep two questionnaires of each respondent in a closed box and only doctor will have access to the questionnaires.  Once doctor will gather 30-40 questionnaires, they will be sent to Nur-Sultan for further analysis and storage. An assigned courier will deliver questionnaire from each city to Nur-Sultan. Questionnaires will be delivered in a sealed folder.  Once questionnaires will be delivered to Nur-Sultan, they will be stored in closed box in PI’s office.  Only complete questionnaires with proper respondent ID will be analyzed for this study.  Data from paper-based questionnaires will be uploaded to computer with the use of Excel software. Once all questionnaires will be uploaded to Excel sheet, data will be imported into STATA16 software and further analyzed. |
| **Inclusion Criteria:** | Women aged between 18 and 70 attending gynecological clinics, and living in one of the cities: Nur-Sultan, Almaty, Aktobe, Oskemen, Pavlodar will be included in the study |
| **Exclusion Criteria:** | Women outside of the age range (18-70) will be excluded from the study |
| **Number of Subjects:** | Approximately 2000 patients will be included in the study. Every doctor will collect around 400 surveys. |
| **Rationale for Number of Subjects:** | The number of patients can be explained by the budget provided to the doctors who will conduct the survey. Each doctor will be paid salary for conducting a survey. |
| **Study Duration:** | The study will be conducted between April 2019 and December 2020. |
| **Risks:** | It is possible that study participants may not:  -feel encouraged to share accurate and honest answers  -feel comfortable providing answers that present themselves in a unfavorable manner  -fully be aware of their reasons for any given answer because of lack of memory and knowledge on the subject |
| **Risk Mitigation:** | In order to avoid the risks outlined above subjects may skip any question they do not wish to answer and/or may withdraw consent from the study at any time without repercussion. |
| **Statistics:** | Statistical analysis will be performed using STATA 16 software. Data analysis will include descriptive statistics consisting of mean values, standard deviations, and frequencies, where applicable. Relationships between categorical variables will be analyzed using Chi-square test with significance value of <0.005. Crude odds' ratio (COR) and adjusted odds ratio (AOR) with 95% corresponding confidence intervals will be calculated in univariate and multivariable logistic regression models. A significance value <0.05 will be used as an indication of association between variables. |

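### The Primary Endpoint row defines awareness of HPV by a question about the HPV vaccine, so no primary outcome as written measures awareness of the virus

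*Protocol*

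**What the plan says.** The Primary Objectives row names HPV awareness and vaccine awareness as separate targets: the study is to "assess the awareness about HPV, the knowledge of HPV as a cause of cervical cancer, and the awareness of HPV vaccination". It also sets out to "identify the factors associated with the awareness of HPV and HPV vaccine".

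The Primary Endpoint row then fixes three binary outcomes with their wording and coding. The first is "awareness of HPV (“Have you ever heard about HPV vaccine?” Yes/No". The second is a true/false statement on HPV infection as the main cause of cervical cancer. The third is "awareness of HPV vaccine (“There is a vaccine against HPV infection.” True/False".

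The Study Design row describes a 25-item patient questionnaire whose topics include "awareness of HPV, awareness of risks of HPV, and awareness of HPV vaccine". It does not give the wording or order of the items. The Statistics row plans crude and adjusted odds ratios from logistic regression.

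**The concern.** The label of the first outcome and the item attached to it describe different things: the label is the virus, the item is the vaccine. A woman who has heard of HPV but not of a vaccine would truthfully answer No and be recorded as unaware of HPV.

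The third outcome already covers the vaccine, so two of the three primary outcomes rest on vaccine items. The second outcome does concern the virus, but it tests agreement with a causal statement and not whether the woman has heard of HPV. No listed outcome therefore measures awareness of the virus, which is the first target in the objectives.

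An analyst following the row would estimate the prevalence of having heard of the vaccine, model its associated factors, and report both as results for HPV awareness. This is not a detail left for a later analysis plan, because the protocol itself fixes the item.

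**Working it through.** **Stated figure.** The only figure that bears on precision is the sample size. The Study Design row has five doctors, and the Number of Subjects row says "Every doctor will collect around 400 surveys". 5 × 400 = 2000, which agrees with "Approximately 2000 patients will be included in the study".

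**The rows side by side.**

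| Place in protocol | Awareness of the virus | Awareness of the vaccine |
|---|---|---|
| Primary Objectives | listed | listed separately |
| Study Design, patient form topics | listed | listed separately |
| Primary Endpoint, first outcome | label only | item asked |
| Primary Endpoint, third outcome | none | label and item |

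**Size of the understatement.** The documents give no awareness figures, so the inputs here are assumptions:
- h = true proportion who have heard of HPV, taken as 0.4 to 0.8.
- s = proportion of those women who have also heard of the vaccine, taken as 0.5 to 0.9.
- Nobody has heard of the vaccine without having heard of HPV.

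The recorded proportion is v = h × s, and the understatement is h − v = h(1 − s). The 95% half-width under simple random sampling is 1.96 × √(v(1 − v)/2000).

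| h | s | v | Understatement (points) | Half-width (points) |
|---|---|---|---|---|
| 0.4 | 0.5 | 0.20 | 20 | 1.75 |
| 0.4 | 0.7 | 0.28 | 12 | 1.97 |
| 0.4 | 0.9 | 0.36 | 4 | 2.10 |
| 0.6 | 0.5 | 0.30 | 30 | 2.01 |
| 0.6 | 0.7 | 0.42 | 18 | 2.16 |
| 0.6 | 0.9 | 0.54 | 6 | 2.18 |
| 0.8 | 0.5 | 0.40 | 40 | 2.15 |
| 0.8 | 0.7 | 0.56 | 24 | 2.18 |
| 0.8 | 0.9 | 0.72 | 8 | 1.97 |

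The understatement exceeds the half-width in every row, and more respondents would not reduce it.

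**Effect on odds ratios.** Assume two groups with true HPV awareness of 0.7 and 0.5. The true odds ratio is (0.7/0.3)/(0.5/0.5) = 2.33. The recorded odds ratio uses 0.7 × s in the first group and 0.5 × s in the second.

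| s, first group | s, second group | Recorded proportions | Recorded odds ratio |
|---|---|---|---|
| 0.9 | 0.9 | 0.63 vs 0.45 | 2.08 |
| 0.6 | 0.6 | 0.42 vs 0.30 | 1.69 |
| 0.5 | 0.7 | 0.35 vs 0.35 | 1.00 |
| 0.8 | 0.5 | 0.56 vs 0.25 | 3.82 |

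In these examples the association is attenuated when s is equal in the two groups. When s differs, it can vanish or be exaggerated.

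**The case against.** The strongest reply is that the row may simply cite the wrong question. The Study Design row lists HPV awareness as its own topic on the patient form, and the form is not shown, so a proper heard-of-HPV item may be on it. This stands, and it limits the conclusion. A reader might infer that the survey cannot estimate HPV awareness at all. The documents do not support that; they show only that the outcome as defined does not measure it. The reply does not remove the contradiction, because the topic list is a second place where the protocol separates what the endpoint row merges.

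A reader might also infer that no primary outcome concerns the virus. That is too strong, since the second outcome concerns HPV infection as a cause of cervical cancer. What is missing is an awareness item.

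A third inference is that asking about the vaccine gives away the answer to the third outcome. That depends on item order, which the protocol does not state, so nothing here rests on it.

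Finally, the percentages are illustrative. If some women report having heard of the vaccine but not of HPV, the net understatement is the share knowing only the virus minus the share reporting only the vaccine.

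**Conclusion.** The Primary Endpoint row is wrong as written. It contradicts the Primary Objectives row and the questionnaire topics in the Study Design row. Followed literally, it yields vaccine awareness and its associated factors under the label of HPV awareness.

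Under the stated assumptions the understatement is 4 to 40 percentage points, against a sampling half-width of about 2 points, and the odds ratios can be biased in either direction. The mismatch is certain from the text. Its size is not, because it depends on two proportions that the protocol does not give. Whether the survey data can still answer the HPV-awareness question depends on the patient form. The point must be settled before analysis because it changes a primary result.

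**What to change.** Check the patient form.

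- **If it already asks whether the respondent has heard of HPV:** correct the Primary Endpoint row to that item before analysis. This costs one sentence.
- **If it does not:** add *Have you ever heard of human papillomavirus (HPV)?* (Yes/No) ahead of the other HPV items, and define the outcome by it. This costs one extra item on a 25-item form and no extra respondents. Placing it first limits cueing from later items, but not from the study information given before the form, if that information names HPV.

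The vaccine-awareness outcome can stay as stated. Any responses already collected without a heard-of-HPV item should be reported as having heard of the vaccine, not as HPV awareness.

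### The item labelled awareness of HPV asks about the HPV vaccine, so it misses its construct and can cue the True/False vaccine-awareness item on the same form

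*Protocol*

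**What the plan says.** The protocol's Primary Endpoint row lists three outcomes. Two matter here:

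- Awareness of HPV is defined by a Yes/No answer to "Have you ever heard about HPV vaccine".
- Awareness of the HPV vaccine is defined by a True/False answer to "There is a vaccine against HPV infection".

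The Study Design row says that respondents complete a 25-item paper questionnaire themselves. Its listed topics end with "awareness of HPV, awareness of risks of HPV, and awareness of HPV vaccine". Neither row fixes an item order or mentions a don't-know answer, and the protocol states no safeguard against one item cueing another. The Study Design row also restricts the analysis to complete questionnaires, while the Risk Mitigation row allows a woman to skip any question.

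**The concern.** There are two linked faults.

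**Label and wording disagree.** A woman who has heard of the virus but not of a vaccine answers No and is counted as unaware of HPV. As written, none of the three outcome items asks whether she has heard of the virus, although the Primary Objectives row names that as something to be estimated and explained.

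**One outcome item presupposes the answer to another.** Asking whether someone has heard of the HPV vaccine implies that it exists. The vaccine outcome then gives credit for agreeing that it exists. If the presupposing item is read first, or if she looks back on the paper form, an unaware woman can score as aware.

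Both parts of the objective are exposed: the proportion aware, and the odds ratios for factors associated with awareness. No later analysis can separate what a woman knew beforehand from what the form suggested to her.

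**Working it through.** **1. The figure in the plan.** The protocol gives no expected awareness, power or precision target. The only figure to reproduce is the sample size: "Every doctor will collect around 400 surveys", with five doctors, gives 5 × 400 = 2000. This agrees with "Approximately 2000 patients will be included in the study". The point does not depend on it, except as a yardstick for sampling error in step 4.

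**2. The two items side by side.**

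| Outcome label | What the item asks | Consequence |
|---|---|---|
| Awareness of HPV (Yes/No) | Whether she has heard of the vaccine | Measures vaccine awareness; implies that a vaccine exists |
| Awareness of HPV vaccine (True/False) | Whether a vaccine exists | Gives the correct answer as the statement to be agreed with |

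The mismatch in the first row can be read directly from the protocol. The cue from the first row to the second depends on item order, or on looking back.

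**3. Effect on the proportion (illustration).** Let p be true awareness and c the share of unaware women who answer True through a cue or a guess. Both are assumptions. Assume also that every aware woman answers True. Then

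observed = p + (1 − p) × c

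| p | c = 0.10 | c = 0.25 | c = 0.50 |
|---|---|---|---|
| 20% | 28% | 40% | 60% |
| 40% | 46% | 55% | 70% |
| 60% | 64% | 70% | 80% |

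For example, 0.40 + 0.60 × 0.10 = 0.46 and 0.40 + 0.60 × 0.50 = 0.70. Over this grid the excess runs from 4 points (64% against 60%) to 40 points (60% against 20%).

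**4. Comparison with sampling error.** At n = 2000 and a proportion of 0.5, treating the women as a simple random sample, the 95% half-width is 1.96 × √(0.25/2000) = 0.022, or about 2.2 points. Even the smallest excess in the grid is larger, and a bigger sample would not reduce it.

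**5. Effect on an odds ratio (illustration).** Take two groups with true awareness of 50% and 30%. The true odds ratio is (0.50/0.50)/(0.30/0.70) = 2.33. With the same c in both groups:

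- c = 0.10: 55.0% v 37.0%, odds ratio 2.08
- c = 0.25: 62.5% v 47.5%, odds ratio 1.84
- c = 0.50: 75.0% v 65.0%, odds ratio 1.62

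If c differs between groups, for instance by education, the bias can go either way.

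**6. What the arithmetic does not isolate.** c mixes cue and guess. If unaware women simply guessed at 50%, p = 40% would already give 0.40 + 0.60 × 0.50 = 70% with no cue at all. The cue's own contribution is (1 − p) times the rise that it causes in c, and the documents do not allow that rise to be estimated.

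**The case against.** The strongest reply is that the cue argument is conditional. The topic list in the Study Design row describes content and is not an item sequence. If the label governs, the word vaccine in the first item is probably a slip, and the cue from that item disappears once the slip is corrected. If the wording governs, the item belongs with the vaccine questions, and no order between it and the True/False statement is given. The magnitude rests wholly on assumed values that plain guessing could also produce. All of this stands. It limits the cue to a risk of unknown size. It does not touch the mismatch between label and wording, nor the fact that a True/False statement containing the right answer credits guesses. The rule on complete questionnaires adds to the second of these: unless complete is read loosely, an unsure woman must answer or be left out.

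A reader might go further and infer that the consent process itself tells every woman that a vaccine exists. The study title names it ("Knowledge and awareness of human papillomavirus infection and human papillomavirus vaccine among Kazakhstani women attending gynecological clinics"), and information precedes the form ("Before participating in the survey prospective respondents will be provided information about research and doctors will read them verbal consent"). The documents do not support that inference. Neither the consent script nor the information letter is shown, and nothing says that the title is read or printed there. For the same reason one cannot say that every respondent is cued, or that the outcome is inflated in all women.

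**Conclusion.** The point holds in a limited form. It is certain, on the protocol's text, that the item for awareness of HPV does not measure its label and that it presupposes the fact on which another primary outcome is scored. It is plausible but not shown that the first item cues the second; that depends on an item order that the protocol leaves open. The size is unknown. At an assumed true awareness of 40%, with 10% to 50% of unaware women answering True, the observed figure would be 46% to 70%, with cue and guess counted together. With equal misclassification across groups, odds ratios move toward 1; with unequal misclassification the direction is open. The change is worth making because it costs almost nothing and bears on named primary outcomes.

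**What to change.** 1. Word the HPV-awareness item about HPV itself, without the word vaccine, and make the Primary Endpoint row match the form. If the form already asks about HPV, this is only a correction to the protocol.
2. Place the True/False vaccine statement before any other item that names an HPV vaccine. Alternatively, score vaccine awareness with a non-leading list item, in which HPV appears among several infections, some with a vaccine and some without. Re-ordering deals with the cue only; the list item also reduces the credit given to guesses.
3. State the order of the outcome items in the protocol.

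The cost is a minor edit of the form and some loss of comparability with surveys that use the current wording. The information given to participants should not be narrowed to avoid cueing. The Study Design row commits to full information: "All the information about the study and participants rights will be stated both orally and on the information letter provided to the participants". The steps above do not need that commitment to be weakened.

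### Two primary outcomes are True/False statements with no stated place for a woman who does not know, so guesses can count as knowledge and blanks may be dropped

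*Protocol*

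**What the plan says.** The Primary Endpoint row of the Protocol lists three outcome variables. Two of them rest on agreement with a single statement. The item on cause reads "knowledge of HPV as a major cause of cervical cancer (“HPV infection is the major cause of cervical cancer.” True/False". The other such item, which follows it in the list, concerns the vaccine and reads "awareness of HPV vaccine (“There is a vaccine against HPV infection.” True/False".

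The Primary Objectives row treats the causal role of HPV and the existence of a vaccine as facts to be known, so 'True' is the answer that scores on both items. The row states no 'Don't know' or 'Not sure' category, no reverse-worded item and no rule for classifying a respondent who does not know.

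Two other rows decide what happens to a blank. Risk Mitigation says that "subjects may skip any question they do not wish to answer". Study Design says that "Only complete questionnaires with proper respondent ID will be analyzed for this study". The word 'complete' is not defined. The patient questionnaire (25 items) is described but not reproduced.

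**The concern.** The first half of the primary objective is to estimate how many women know these facts. A woman who does not know has three courses open to her under the stated definition.

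- She ticks 'True' and is counted as knowing.
- She ticks 'False' and is correctly counted as not knowing.
- She leaves the item blank and, on a literal reading of the completeness rule, leaves the analysis.

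The first adds false positives. The third removes true negatives. Both push the estimate upward, and nothing in the definition pushes it back. A tendency to agree with statements would add to this: under Study Design the woman's own doctor invites her and takes the form back, a setting that may encourage agreement.

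The second half of the objective is to find factors associated with knowledge. Guessing misclassifies the outcome of the logistic models planned under Statistics, and adjusting for covariates does not undo that.

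**Working it through.** **Inputs from the Protocol.** The True/False format with 'True' scoring (Primary Endpoint); the right to skip (Risk Mitigation); analysis of complete questionnaires only (Study Design); and the sample size, "Approximately 2000 patients will be included in the study. Every doctor will collect around 400 surveys". Five doctors at 400 each give 5 × 400 = 2000, which matches. The number is set by budget, so there is no power or precision calculation to reproduce.

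**Assumptions.** k is the share who truly know, and g is the chance that a woman who does not know ticks 'True'. The Protocol gives neither, so ranges are shown. Women who know are taken always to tick 'True'.

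**1. Prevalence when nobody skips.** Reported share = k + (1 − k)g, so the bias is (1 − k)g. With k = 0.30:

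- g = 0.25: 0.30 + 0.70 × 0.25 = 47.5%
- g = 0.5: 0.30 + 0.70 × 0.5 = 65%
- g = 0.7: 0.30 + 0.70 × 0.7 = 79%

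At g = 0.5, k = 20% is reported as 60% and k = 40% as 70%. For comparison, the 95% half-width at 2000 women is at most 1.96 × √(0.25/2000) = 2.2 percentage points. Even the smallest bias above (17.5 points) is far outside sampling error, and a larger sample would not reduce it.

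**2. Prevalence when some skip and are dropped.** Take k = 0.30, g = 0.5, and let half of the non-knowers leave the item blank. Of 2000 women, 600 know and 1400 do not. Of those 1400, 700 are dropped and 700 stay, of whom 350 tick 'True'. The analysis then has 1300 women and 600 + 350 = 950 'True' answers: 950/1300 = 73%, against 65% with no skipping.

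**3. Odds ratios when g is equal in both groups.** The reported odds are (o + g)/(1 − g), where o is the true odds k/(1 − k). The reported odds ratio is therefore (o₁ + g)/(o₀ + g), which lies closer to 1 than o₁/o₀ for any g above 0. For a true contrast of 30% against 50%, o₀ = 0.4286, o₁ = 1 and the true odds ratio is 2.33:

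- g = 0.25: 1.25/0.6786 = 1.84
- g = 0.5: 1.5/0.9286 = 1.62
- g = 0.7: 1.7/1.1286 = 1.51

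**4. Odds ratios when g differs between groups.**

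- Equal knowledge (30% in both), g = 0.6 against 0.5: reported 72% against 65%, odds ratio (0.72/0.28)/(0.65/0.35) = 1.38 where the truth is 1.
- True 50% against 30%, g = 0.7 in the first group and 0.5 in the second: 85% against 65%, odds ratio 5.667/1.857 = 3.05, above the true 2.33.
- The same contrast with g = 0.25 in the first group and 0.5 in the second: 62.5% against 65%, odds ratio 1.667/1.857 = 0.90, on the wrong side of 1.

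The direction of the bias in the associations therefore depends on who guesses, which the stated format does not record.

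**The case against.** The strongest reply is that the questionnaire is not shown. The True/False labels stand in a list of outcome variables, and they fit a two-level outcome derived for logistic regression as well as they fit two printed boxes. This stands. A reader might infer that the form forces a choice and has no 'Don't know' box, but the Protocol does not establish that. The Risks row does not settle it either: its worry that women may not "fully be aware of their reasons for any given answer because of lack of memory and knowledge on the subject" concerns the reliability of answers, not the options printed on the form.

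It can also be said that coding a third answer belongs in an analysis plan, which may exist. That would hold if the Protocol were silent. Here it states the response levels of two primary outcomes and a completeness rule, and followed as written these already determine a biased result.

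'Complete' could mean that the form was finished and returned, not that every item was answered. On that reading skippers need not be lost and step 2 of the working falls away, but step 1 remains. The loss of skippers is in any case a missing-data effect, additional to the effect of the response format.

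Two further inferences are tempting and go too far. One is that the odds ratios must shrink toward 1, which holds only if g is equal across groups. The other is that the inflation is 35 points, which is the result for k = 30% and g = 0.5; other assumed values give other results.

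That a True/False statement reveals its own answer is common to such items and is not pressed here.

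**Conclusion.** The point holds for the outcomes as the Protocol defines them. Two of the three primary outcomes have no stated category for not knowing, and the skip and completeness rules give such a woman no safe alternative. Reported prevalence is biased upward whenever some non-knowers tick 'True' or are dropped. If 30% truly know, the reported figure runs from 47.5% to 79% for g between 0.25 and 0.7. Associations are attenuated under equal guessing and unpredictable under unequal guessing.

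The direction for prevalence rests on the literal definition. The size rests on assumed k and g. If the printed form already offers 'Don't know', the defect reduces to an endpoint definition that omits this category and its coding.

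**What to change.** For both statements, offer True / False / Don't know. If the form already has the third box, say so in the Primary Endpoint row. Add one coding sentence there, for example: *the outcome is 1 if the respondent ticks 'True' and 0 if she ticks 'False' or 'Don't know'*. Add to Study Design that a 'Don't know' tick is an answer and does not make a questionnaire incomplete.

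Keep a single definition of vaccine awareness. The first outcome, "awareness of HPV (“Have you ever heard about HPV vaccine?” Yes/No", asks about the vaccine under a label about the virus. That mismatch needs its own correction and should not be used here to create a second vaccine-awareness outcome.

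The cost is one tick-box on two items and two sentences, or the sentences alone if the box exists. Reported knowledge will be lower. Some guessing will remain, because the box reduces g but need not bring it to zero. Any forms already collected in a two-option format need a separate or flagged analysis.

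### Patients answer right after the gynecology visit with no 'before today' limit, so anything said in the visit can be counted as prior awareness; the size is unknown

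*Protocol*

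**What the plan says.** The Study Design row of the protocol fixes the order of events. Recruitment comes last in the visit: "At the end of the appointment doctors will propose their patients to participate in the study". Study information and consent follow: "Before participating in the survey prospective respondents will be provided information about research and doctors will read them verbal consent". Then come the forms: "Doctors and patients will fill out the questionnaires right after the appointment".

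The Primary Endpoint row prints three outcome items:

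- awareness of HPV: "Have you ever heard about HPV vaccine?” Yes/No"
- knowledge of HPV as a cause: "HPV infection is the major cause of cervical cancer.” True/False"
- awareness of the vaccine: "There is a vaccine against HPV infection.” True/False"

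None carries a time limit. The patient form also covers "awareness of screening for cervical cancer, whether the patient had gone through screening for cervical cancer, awareness of HPV, awareness of risks of HPV". The doctor form is described as 30 items on socio-demographic characteristics, lifestyle and past gynecological disease; what was discussed at the visit is not among the listed contents. The Risks row mentions honesty, unfavorable answers and limited memory or knowledge, but not information received at the visit.

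**The concern.** The objective is to describe what women attending these clinics know and to find factors associated with it. The form is filled in straight after a consultation in which some of the same facts may have been raised. If the doctor mentions the vaccine, or says that HPV causes cervical cancer, a woman who did not know this an hour earlier answers correctly and truthfully. She cannot then be told apart from a woman who already knew.

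Two results could suffer. The proportions aware or knowledgeable can be too high. The odds ratios can also be partly distorted if the chance of such a discussion depends on a factor under study, such as doctor (and so city) or gynecological history. Adjusting for city would not remove differences that arise within a city. A larger sample would not help, because this is a matter of measurement. If visit content is not recorded, no later analysis can separate the two groups, so the point cannot be left to an analysis plan.

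**Working it through.** **The plan's own figure.** Five doctors × about 400 surveys = 2000, which matches the Number of Subjects row. The protocol gives no expected proportion, effect size or power.

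**Inputs.** n = 2000 is from the protocol. Two inputs are assumed because the protocol gives neither: p, the proportion who knew the fact before the visit, and f, the share of the remaining women who learn it at the visit and answer accordingly. f refers to the specific fact in each item, so it can differ between the three outcomes.

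**Effect on a proportion.** Observed = p + f(1 − p), so the bias is f(1 − p). At p = 0.40:

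- f = 0.05: 0.40 + 0.05 × 0.60 = 0.43, bias +3 points
- f = 0.10: 0.40 + 0.10 × 0.60 = 0.46, bias +6 points
- f = 0.20: 0.40 + 0.20 × 0.60 = 0.52, bias +12 points

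The 95% half-width at n = 2000 is 1.96 × √(0.40 × 0.60 / 2000) = 0.0215, and at most 1.96 × √(0.50 × 0.50 / 2000) = 0.0219, so about 2.2 points. The bias equals the half-width when f ≈ 0.0216 / 0.60 ≈ 0.036. Below about 3.6% it is within sampling error.

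Other values of p:

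| p | f = 5% | f = 10% | f = 20% | 95% half-width |
|---|---|---|---|---|
| 30% | +3.5 | +7 | +14 | 2.1 to 2.2 |
| 50% | +2.5 | +5 | +10 | 2.2 |
| 70% | +1.5 | +3 | +6 | 1.9 to 2.0 |

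The half-width treats the women as a simple random sample. It is only a yardstick here.

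**Effect on an odds ratio.** Take two groups with the same true awareness of 50% but different f. The chance of p < 0.05 (two-sided) is Φ[(d − 1.96·SE₀)/SE₁], where d is the difference in observed proportions and SE₀ and SE₁ are its pooled and unpooled standard errors. Group sizes are 400 v 400 (one doctor's quota against another's) and 1000 v 1000 (an even split of the sample).

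- f = 10% v 20%: observed 55% v 60%; OR = (0.60/0.40)/(0.55/0.45) = 1.23; chance of p < 0.05 is 30% and 62%.
- f = 10% v 30%: observed 55% v 65%; OR = (0.65/0.35)/(0.55/0.45) = 1.52; chance of p < 0.05 is 82% and 99.6%.

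A difference in discussion alone can thus produce an association. Whether it would probably do so depends on a contrast in f that the protocol does not allow one to estimate.

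**The case against.** The strongest objection is that the protocol nowhere says what is discussed at these visits, how often HPV is raised, or why the women attend. A reader might infer that awareness is biased upward and that associations with gynecological history, screening or clinic are spurious. The documents do not support that. If f is small, the bias is lost in sampling error. Women with a gynecological history or past screening may truly know more through earlier care, so such associations may be real and at most partly inflated. This objection stands, and it limits the point to a possible bias of unknown size.

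Second, merely hearing the word HPV need not change any printed item. Two items concern the vaccine and one concerns HPV as the major cause, so the doctor would have to mention those facts. This also stands, and f must be read accordingly.

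Third, only three items of the 25-item patient form are printed and none of the 30-item doctor form. A heading with a time limit, or an item on visit content, cannot be ruled out. The point therefore applies to the forms as the protocol describes them, and checking the forms would settle it.

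Fourth, a reader might see an incentive in the doctors' pay. The protocol pays a salary for conducting the survey and ties nothing to the answers, so this adds nothing.

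None of this changes the order of events or the wording of the items. The doctors' training is described as "The doctors will be trained how to recruit the participants and how to conduct a survey, and how to store completed questionnaires", which does not touch the issue.

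**Conclusion.** The point holds as a weakness of measurement timing. The protocol fixes completion after the visit, prints outcome items without a time limit, and describes no record of visit content. If the vaccine or the HPV–cancer link is mentioned in the visit, awareness and knowledge can be inflated; if that happens more in some groups than in others, the odds ratios can be partly distorted.

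The size is unknown. With p = 40% assumed, the bias is +3 to +12 points for f from 5% to 20%, and it is within sampling error for f below about 3.6%. Both p and f are assumptions. The case for acting is that the remedy is cheap before data collection, and the missing information cannot be recovered afterwards.

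**What to change.** **Preferred, where feasible.** If the doctor can give the study information and take verbal consent at the start of the visit without extra staff, have the patient complete her form before the consultation. The doctor form can stay where it is.

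**Otherwise**, make three small changes:

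1. Head the knowledge section with an instruction that fits the True/False statements as well as the 'ever heard' item, for example: *Answer according to what you knew before today's visit.*
2. Add one item to the doctor form: *HPV, cervical screening or HPV vaccine discussed with the patient today: Yes/No.*
3. Report the primary analyses by that item as a sensitivity analysis. State that the No group is a selected subset, since discussion may depend on clinical history, and is not a clean estimate of prior awareness.

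**Cost.** The first option changes clinic flow: the patient form takes about 15 minutes, and the doctors are the only people named as recruiting and reading consent. The second costs one instruction and one item, and relies partly on recall. Under either option, study information that names HPV or the vaccine, as the study title does, may still cue answers. Its text is not shown and should be checked for this.
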